### Sample size

Considering a confidence level of 95%, an incidence rate of 93.7 per 100,000 inhabitants in the municipality of Porto Alegre [9], and an acceptable difference of 60.0 per 100,000 inhabitants, it is estimated that testing 10,000 individuals will be necessary to obtain an accurate prevalence of syphilis in the municipality. This sample will serve as the basis for the inclusion of patients in the clinical trial.

For the randomized clinical trial, another sample size calculation will be considered. Using a previous article in which 16.5% of the participants who were diagnosed with syphilis received appropriate treatment and 55.9% received inappropriate treatment as a reference, it is expected that at least half of the latter group will eventually receive proper treatment, for a total of 44.45% receiving appropriate treatment [17]. Thus, considering a sample size calculation to detect differences in the proportions of adequate treatments between groups, using a 95% confidence level, 80% power, and a maximum loss rate of 20%, 51 participants in each study group will be needed.

The primary goal of the study is to compare treatment adherence and follow-up among the three parallel study arms. The groups will be compared as a whole, and if relevant, pairwise analysis will be conducted. Such comparisons will be performed using the chi-square test and adjusted residuals when necessary. We will investigate the association between treatment

adherence and sociodemographic, sexual health, and sexual behavior variables as secondary outcomes. The association will be estimated by calculating crude and adjusted odds ratios (ORs) using logistic regression, also addressing confounding variables. Intention-to-treat analysis will be used to assess the clinical effectiveness of the intervention.

We anticipate a minimal number of missing values given that the study variables will be collected by trained researchers. However, data quality analysis will be applied to identify inconsistencies and missing data, and meetings with the researchers will be conducted to discuss missing data and prevent further inconsistencies.

A statistical significance level of 0.05 will be adopted for all statistical analyses. R software, version 4.0.3, will be used for the analysis.

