### Study procedures

A paper-based questionnaire to collect sociodemographic, behavioral, and health information will be administered to all participants to check eligibility, and a rapid test for syphilis will be performed. All participants with a positive test result will undergo confirmatory testing. Upon the receipt of confirmatory test results, the participants will be invited to take part in the clinical trial, and a web-based questionnaire will be used to collect information such as age, sex, social class, education level, alcohol consumption, tobacco and drug use, risk for syphilis, history of hepatitis and other sexually transmitted infections (STIs), number of sexual partners, type of sex and condom use. The main objective of the trial is to test strategies to improve adherence to follow-up. Overall, to increase awareness regarding syphilis, all participants will receive informative folders on syphilis, HIV, and hepatitis prior to randomization. Adherence will be monitored by the number of accesses to the application and by successful telephone calls.

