#### Randomization and blinding

Patients will be randomized at a ratio of 1:1:1 among the three intervention arms: follow-up by telephone, follow-up using a smartphone game, or follow-up with usual care in the public health system. Random allocation will be performed in blocks with variable sizes, stratified by participants with and without smartphone access. Randomization will be performed using R software [18]. Individuals who have access to a smartphone will be randomly assigned to any of the 3 groups, while individuals without access to a smartphone will be randomly assigned to one of only two groups: the telephone follow-up group or the control group.

An independent statistician will be responsible for computerized randomization (R software [18]) but will not be involved in the determination of participant eligibility, assessment or implementation of the interventions. Blinding will be applied to minimize bias. Allocation concealment as the person responsible for the randomization will be applied to the randomized group only after the participants have been recruited, which will occur after baseline measurements are completed. Researchers responsible for the follow-up by telephone intervention will not have access to performance and evaluation data. Only the biostatistician will have access to the data stored in the data entry system, minimizing investigator influence.

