### Outcome assessment

Compliance with treatment for those in the mobile app arm will be assessed according to the uploaded game data provided by the participant and use of the app during the study period. Adherence to treatment for those receiving telephone follow-up will be assessed through routine phone calls and questionnaire questions about the date of examination and treatment. Adherence in the usual care arm will be assessed by information collected from the participant's medical record at their referral health unit. The primary outcome will be the percentage of the participants who finish all three doses of penicillin in the 3 weeks. The secondary outcome will be the percentage of participants who completed VDRL tests at 3, 6, and 12 months. We also evaluated the number of sexual contacts informed by each participant. The outcomes will be evaluated by self-declaration and by contacting the healthcare unit where the participants made treatment and follow-up.

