### Statistical analyses

Descriptive analysis will be performed to characterize the study population. The categorical variables will be summarized by absolute frequencies and percentages, while continuous variables will be described as the means and standard deviations or medians and interquartile ranges.

To compare proportions, the chi-square test and Fisher's exact test will be used. Student’s *t* test or the nonparametric Mann–Whitney test will be used to compare continuous variables.

The primary goal of the study is to compare treatment adherence and follow-up among the three parallel study arms. We will investigate the association between treatment adherence and sociodemographic, sexual health, and sexual behavior variables as secondary outcomes. The association will be estimated by calculating crude and adjusted odds ratios (ORs) using logistic regression. Intention-to-treat analysis will be used to assess the clinical effectiveness of the intervention.

A statistical significance level of 0.05 will be adopted for all statistical analyses. R software, version 4.0.3, will be used for the analysis [18].

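### The primary arm comparison uses a covariate-free chi-square test and leaves unused both the smartphone-access stratum and baseline variables measured before allocation: a missed efficiency, not an error in the sample size

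*Protocol article*

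**What the plan says.** The primary outcome is binary (Outcome assessment): "The primary outcome will be the percentage of the participants who finish all three doses of penicillin in the 3 weeks".

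The Sample size section sets the order of testing, "The groups will be compared as a whole, and if relevant, pairwise analysis will be conducted", and then the method: "Such comparisons will be performed using the chi-square test and adjusted residuals when necessary". The Statistical analyses section agrees: "To compare proportions, the chi-square test and Fisher's exact test will be used". None of these tests takes a covariate or a stratum. Adjusted residuals are cell diagnostics for a contingency table, not covariate adjustment.

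Under Study procedures, "a web-based questionnaire will be used to collect information such as age, sex, social class, education level, alcohol consumption, tobacco and drug use", along with STI history and sexual behaviour. Randomization and blinding places allocation after recruitment, "which will occur after baseline measurements are completed". The same section stratifies randomisation by smartphone access and allocates people without a smartphone only to telephone or usual care.

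Crude and adjusted logistic regression is planned in both statistical passages. Its stated purpose is the association of adherence with sociodemographic, sexual health and sexual behaviour variables, as secondary outcomes. Arm is not named as a term.

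**The concern.** The protocol collects candidate predictors of completion before allocation and plans logistic models on them, but does not use them for the arm effect. If some of them predict completion, adjusting for them would raise power and narrow the intervals for the arm contrasts, with no new data and no extra participants. The trial is small, so a few points of power are worth having.

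The one factor that the design itself singles out, smartphone access, is also missing from the comparison. It deserves attention beyond precision. Since people without a smartphone cannot enter the app arm, a pooled comparison of that arm with either other arm is not a comparison of like with like.

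**Working it through.** **1. Reproduce the plan's sample size.** The inputs are from the Sample size section: "16.5% of the participants who were diagnosed with syphilis received appropriate treatment", so p1 = 0.165; p2 = 0.165 + 0.559/2 = 0.4445; 95% confidence; 80% power; 20% loss; 51 per arm. A two-sided 0.05 level is assumed, because sidedness is not stated.

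n = [1.96·√(2·p̄·q̄) + 0.8416·√(p1·q1 + p2·q2)]² / (p2 − p1)²

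With p̄ = 0.30475 and p2 − p1 = 0.2795, n = (1.276 + 0.522)² / 0.0781 = 41.4, so 42 evaluable per arm. Then 42/0.8 = 52.5 (53), or 42 × 1.2 = 50.4 (51). The arcsine formula gives 40.45/0.8 = 50.6 (51). The stated 51 therefore fits an unadjusted two-arm comparison.

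**2. Crude power.** Power = Φ{[0.2795·√n − 1.276] / 0.620}. After 20% loss, 51 × 0.8 = 40.8, about 41 per arm, which gives 79.6%. With all 51 analysed it is 87.7%.

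**3. Effect of adjustment, by formula.** Replace n by n/(1 − R²), where R² is the share of outcome variance explained by the covariates. R² is not in the document; the values below are assumptions.

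| R² | Power at 41 per arm | Evaluable per arm for 80% power |
|---|---|---|
| 0 | 79.6% | 42 |
| 0.05 | 81.7% | 40 |
| 0.10 | 83.8% | 38 |
| 0.20 | 87.9% | 34 |

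**4. Effect of adjustment, by simulation.** Settings: 3,000 runs each, 41 per arm, rates 16.5/44.45/44.45%, three standard-normal covariates, and the logistic score test for arm against Pearson's chi-square. The c-statistics are assumptions.

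| Combined logit slope (c-statistic) | Pairwise: crude → adjusted | Overall 2-df: crude → adjusted |
|---|---|---|
| 0 (0.50) | 79.0 → 79.5% | 82.2 → 82.2% |
| 0.5 (0.64) | 79.2 → 80.6% | 82.0 → 83.9% |
| 0.8 (0.70) | 80.1 → 84.0% | 82.5 → 87.0% |
| 1.1 (0.76) | 79.7 → 86.1% | 82.1 → 90.1% |

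The Monte Carlo standard error of a power near 80% is √(0.8 × 0.2/3000) = 0.7 points, and repeat runs differed by up to about 1.6 points. Type I error across runs was 4.6–6.4% adjusted and 4.0–6.3% crude. In a separate two-arm simulation, the standard error of the standardised risk difference fell by about 1%, 4% and 8% at c-statistics of 0.64, 0.70 and 0.76.

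**5. Room for covariates.** If both interventions reach 44.45%, expected completers are 41 × (0.165 + 0.4445 + 0.4445) = 43 after loss, and 51 × 1.054 = 54 without loss.

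**6. Smartphone access, an illustration with assumed rates.** Suppose 20% lack a smartphone, and completion is 30% without one and 45% with one, whatever the arm. Smartphone holders split three ways (80/3 = 26.7% of the total per arm), and the others split two ways (10% per arm). In the telephone and usual-care arms, 10/36.7 = 27.3% lack a smartphone, so their completion is 0.727 × 45 + 0.273 × 30 = 40.9%. The app arm shows 45%, an apparent benefit of about 4 points with no true effect.

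**The case against.** The chi-square is a valid test between comparably allocated groups, it is the test that the trial was sized for, and it delivers about 80% power on the plan's own inputs. All of that stands. A reader might infer that the sample size is wrong or the trial underpowered; step 1 shows that it is not. Nor is the power necessarily tight: 41 per arm assumes that the full maximum loss occurs and that those participants drop out of the analysis, whereas the plan is intention-to-treat, and 51 per arm gives 87.7%.

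A reader might also infer that the baseline variables are known predictors, so that power is certainly being given up. The document does not say so. It makes their association with adherence a secondary question, and no passage states that any of them predicts three-dose completion. The gain is conditional: about one to two points at a c-statistic of 0.64, and nothing at 0.50. Likewise, chance imbalance in age or education does not invalidate a crude test, whose error rate already allows for it.

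The simulation is favourable to adjustment. It uses independent normal covariates, a correctly specified model and no missing values. Power was not corrected for the slightly higher type I error, so part of a small gain may come from that. It also did not include the smartphone stratum.

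Finally, an analysis plan that is not shown could add an adjusted analysis, and arm is not ruled out of the planned logistic models. But the article does not leave the arm comparison open: it names the test, and the logistic models are described for another purpose.

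**Conclusion.** The point holds as a missed efficiency. The primary comparison omits the stratification factor and potentially prognostic variables that are available before allocation. At 41 analysed per arm, adjustment is worth about 0 to 8 power points over the assumed range of c-statistics (0.50 to 0.76), and about 8 points at an assumed R² of 0.20. With uninformative covariates the loss is within simulation noise, so the change can be justified without knowing the prognostic strength.

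It does not rescue every contrast. For app versus telephone at an assumed 44.45% versus 60%, power is 28.9% crude and 34.9% at R² = 0.20.

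Smartphone access is the best-founded term. The case for it rests on the allocation rule, which is stated; the size of any bias in app contrasts rests on assumed rates. Telephone versus usual care is not affected in this way, since both strata can enter both arms.

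**What to change.** Make the primary analysis a logistic model for three-dose completion with terms for arm, the smartphone-access stratum and about two or three baseline covariates fixed before any outcome is seen (for example age, education and STI history, one degree of freedom each). Test arm by the score or likelihood-ratio test. Report marginal risk differences with 95% confidence intervals for the three pairwise contrasts.

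Restrict contrasts involving the app arm to participants with smartphone access, because the others could not be allocated to it. Use both strata for telephone versus usual care. A single model on all randomised participants without the smartphone term would be more precise but would leave the app contrasts confounded. Keep the crude chi-square as a supporting analysis.

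The cost is a sentence or two in the analysis section and a few lines of R, with no new data. The downsides are that the covariate list must stay short, given about 43 to 54 expected completers; that type I error may be slightly higher, up to about 6% in simulation; and that app contrasts use fewer telephone and usual-care participants, although those left out carry no randomised information about the app.

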### Study procedures

A paper-based questionnaire to collect sociodemographic, behavioral, and health information will be administered to all participants to check eligibility, and a rapid test for syphilis will be performed. All participants with a positive test result will undergo confirmatory testing. Upon the receipt of confirmatory test results, the participants will be invited to take part in the clinical trial, and a web-based questionnaire will be used to collect information such as age, sex, social class, education level, alcohol consumption, tobacco and drug use, risk for syphilis, history of hepatitis and other sexually transmitted infections (STIs), number of sexual partners, type of sex and condom use. The main objective of the trial is to test strategies to improve adherence to follow-up. Overall, to increase awareness regarding syphilis, all participants will receive informative folders on syphilis, HIV, and hepatitis prior to randomization. Adherence will be monitored by the number of accesses to the application and by successful telephone calls.

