#### Strategy 3: Conventional follow-up

The conventional strategy involves compulsory notification by a healthcare professional, and the patient is directed to seek treatment and follow-up at the primary health care unit closest to his or her home. The outcomes will be accessed by reviewing data from the public health records.

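### App use is named as a basis for judging treatment compliance in the app arm, although the primary outcome is completion of three penicillin doses

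*Protocol article*

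**What the plan says.** Outcome assessment fixes the endpoint: "The primary outcome will be the percentage of the participants who finish all three doses of penicillin in the 3 weeks". The same section then gives each arm its own way of judging adherence or compliance:

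- **App arm:** compliance with treatment is "assessed according to the uploaded game data provided by the participant and use of the app during the study period".
- **Telephone arm:** adherence is "assessed through routine phone calls and questionnaire questions about the date of examination and treatment".
- **Usual care:** adherence is taken from the medical record at the referral health unit. Strategy 3 adds: "The outcomes will be accessed by reviewing data from the public health records".

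The section closes by naming two sources for the outcomes, without distinguishing arms: self-declaration and contact with the health unit.

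Study procedures states: "Adherence will be monitored by the number of accesses to the application and by successful telephone calls". Shortly before that, the same section uses the word for the behaviour the trial wants to change: "The main objective of the trial is to test strategies to improve adherence to follow-up".

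Sample size and Statistical analyses both make the comparison of treatment adherence and follow-up between arms the primary goal. Both also plan logistic models of treatment adherence. Neither says in so many words that this variable is the three-dose outcome.

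**The concern.** Opening the app shows that a participant was reached by the randomised strategy. It does not show that an injection was given. If app use counts towards compliance with treatment, the app arm gets credit for delivering its own intervention, and a participant who plays but is never injected can be scored as a success. Usual care has no app and so cannot gain in this way.

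The error would fall in the arm that the Introduction expects to do best, and in the variable that carries the primary comparison. The logistic models of treatment adherence would inherit it. An app with no effect on treatment could then appear effective.

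**Working it through.** **1. Does the dose-based endpoint drive the design?** Inputs from Sample size: 16.5% and 44.45% adequately treated, 95% confidence (two-sided 0.05 assumed), 80% power, 20% loss. With pooled variance, no continuity correction and p̄ = (0.165 + 0.4445)/2 = 0.30475:

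n = [1.960·√(2·p̄·(1 − p̄)) + 0.842·√(0.165·0.835 + 0.4445·0.5555)]² / (0.4445 − 0.165)² = 41.4, so 42 per arm.

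42 × 1.2 = 50.4, so 51, which is the stated figure. (Dividing by 0.8 gives 53; that is not the point here.) The trial is sized on proportions adequately treated, not on counts of contacts.

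**2. Can app use build up without an injection?** Under Strategy 2, a phase is passed once the doses are taken and the VDRL test is completed, so game progress is tied to treatment. But coins are earned by reading STI information and reporting on partners, and the first phase is open to all participants whatever their rapid test result. App use is therefore possible with no dose given. Outcome assessment lists it as an element additional to the uploaded game data.

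**3. How large could the effect be?** This is an illustration. Let e be the fraction of app-arm non-completers scored adherent because of app use; **e is an assumption and is not in the document**. With no true effect and a common completion rate p, the apparent app-arm rate is p + e(1 − p):

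- p = 16.5%: 24.9%, 33.2%, 41.6% for e = 10%, 20%, 30%
- p = 44.45%: 50.0%, 55.6%, 61.1%

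The false-positive probability is the sum of the two binomial probabilities over all outcome pairs in which the Pearson chi-square (two-sided 0.05, no continuity correction) is significant in favour of the app over usual care. The nominal value in that direction is 2.5%.

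| Base rate | n per arm | e = 10% | e = 20% | e = 30% |
|---|---|---|---|---|
| 16.5% | 51 | 17.8% | 50.7% | 81.4% |
| 16.5% | 41 | 15.4% | 42.3% | 72.0% |
| 44.45% | 51 | 9.2% | 22.3% | 42.2% |

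The 41 is 51 × 0.8 = 40.8, rounded up. At e = 5%, base rate 16.5% and 51 per arm, the value is 7.6%.

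**4. Does the planned order of testing remove it?** Sample size compares the groups as a whole first and pairwise if relevant. Requiring a significant three-arm chi-square as well, with the telephone arm at the base rate and 51 per arm, gives about 12%, 44% and 78% at 16.5%, and 5%, 14% and 31% at 44.45%. The inflation is smaller but remains.

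**The case against.** The strongest reply is that the endpoint is stated once and clearly as three doses, that the sample size agrees with it, and that no sentence gives a rule turning app opens into adherence. On this view the app-use phrase is a loosely worded information source beside game data that are tied to doses, and the health unit is contacted anyway. Most of this stands. It limits the point to the wording of the app-arm assessment. It does not remove the point, because app use is named there as a basis for compliance with treatment, and the section does not say what happens when app use and the health unit disagree.

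Three stronger readings are tempting, and the documents do not support them:

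- **That adherence is defined as contact with the intervention.** Study procedures says it is monitored by accesses and calls. That can be read as a process measure, and counts that exist in only two arms could hardly be the endpoint of a three-arm comparison. The sentence is still unqualified, and the section uses the same word for the target behaviour.
- **That usual care has no adherence value.** This is true only of accesses and calls. Outcome assessment and Strategy 3 both give usual care a records source.
- **That the telephone arm is credited for answered calls.** Outcome assessment uses the calls together with questions on the dates of examination and treatment; it does not score the number answered.

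On size, e has no basis in the document. The 16.5% is a previous article's figure for diagnosed participants, not a stated usual-care rate.

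**Conclusion.** The point holds in a limited form. The plan has a dose-based primary outcome, but its app-arm assessment of compliance includes a measure of exposure to the app, and the monitoring sentence in Study procedures does not separate engagement from treatment. Where app use adds to the evidence for compliance, the resulting error can only favour the app.

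The size is conditional. With no true effect, 51 per arm and a pairwise test, the chance of falsely favouring the app is about 18% to 81% at a base rate of 16.5%, and about 9% to 42% at 44.45%, as e runs from 10% to 30%. If app use is never in fact scored, e is zero and there is no inflation. The documents do not show that misclassification will occur, only that the text as written permits it in the primary comparison.

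**What to change.** 1. In Outcome assessment, remove use of the app from the sentence on compliance with treatment in the app arm.
2. In Study procedures, label app accesses and successful calls as process (engagement) measures, reported within their own arm.
3. In Sample size and Statistical analyses, state that treatment adherence in the between-arm tests and logistic models is the primary outcome (three doses finished in the 3 weeks, yes or no), and that no engagement measure counts towards it.
4. State that this outcome is evaluated in all three arms from the sources named at the end of Outcome assessment, self-declaration and the health unit, and bring the arm-specific sentences into line.

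Items 1 to 3 are wording only: engagement data are still collected and reported. Item 4 applies sources that the protocol already names to every arm. The sample size of 51 per group does not change.
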